## Abstract

**Background:**

Environmental enteropathy (EE) is a highly prevalent subclinical inflammatory intestinal disorder associated with growth failure, impaired neurocognitive development, poor response to oral vaccines, and micronutrient deficiencies. However, EE research and clinical trials are hampered by the lack of non-invasive tools for measuring intestinal function in detail. This study aims to develop new tools for the measurement of multiple domains of gut functional capacity.

**Methods:**

The GI TOOLS project is a cross-sectional study that will recruit adults aged 18-65 years with EE in Lusaka, Zambia. Each participant will undergo assessment of gut functional capacity using novel near-point-of-care tools and provide multiple samples for detailed laboratory analyses. Participants will also undergo endoscopy for collection of duodenal biopsies. Novel techniques include stable isotopes approaches to measuring digestion, absorption, and bidirectional transmucosal amino acid flux, a non-invasive fluorescence tool for real-time evaluation of gut permeability, and assessment of reverse permeation of intravenous antibiotics to be carried out separately in Zimbabwe. Stool and duodenal microbiome sequencing using MinION sequencing, metabolome analysis applied to plasma and intestinal fluids, blood immune cell phenotyping,
*in vitro* epithelial barrier models, and duodenal immunohistochemistry will also be used to explore EE in depth. These will all be integrated with gold standard histology and mucosal morphometry, alongside lactulose permeation data, and stool and plasma biomarker analysis. The protocol has been approved by ethics committees and regulators in Zambia, Zimbabwe, and the UK. Participants will give informed consent before they can participate

**Anticipated outcomes:**

Based on this extensive phenotyping, tests will be developed which can be simplified and refined for use in adults and children with EE, and for clinical trials. Findings from this project will be disseminated through in-person meetings with caregivers and regulatory bodies, presentations at conferences and in peer-reviewed journals.

## Introduction

The gastrointestinal tract is a critical organ, simultaneously orchestrating digestion, absorption, and excretion of gut contents whilst providing a physical barrier between the external environment in the gut lumen and body tissues, creating conditions to tolerate dietary antigens and the gut microbiome.
^
1
^ However, measurement of these intestinal functions, which we refer to hereafter as gut functional capacity, is currently crude and imprecise. There is an urgent need to develop improved tools for the evaluation of a broader range of intestinal functions in studies of pathophysiology and clinical trials in both adults and children.
^
1
^ Following a golden age of research on human intestinal digestion and absorption in the 1970s and 1980s, work on gut physiology has slowed. Current gold-standard approaches to assess gut functional capacity, such as the lactulose-mannitol (or lactulose-rhamnose) test or endoscopy, are time- and labour-intensive or measure only one aspect of intestinal dysfunction, such as its permeability to molecules which normally are excluded from uptake in the healthy state.

Environmental enteropathy (EE) is a highly prevalent subclinical inflammatory intestinal disorder that is associated with exposure to unsanitary conditions and poor nutrition. In children, it is associated with growth failure, impaired neurocognitive development, and poor response to oral vaccines. EE is frequently associated with undernutrition. In moderate undernutrition, limited nutrient bioavailability, pathogen pressure, and gut barrier dysfunction can lead to impaired linear growth (stunting), impaired vaccine response and cognitive deficits in children.
^
2
^ In acute undernutrition, mortality remains unacceptably high, particularly those hospitalised with severe acute malnutrition (SAM).
^
3
^
^,^
^
4
^ Both stunting and incomplete recovery from SAM in childhood embed life-long and intergenerational health consequences which detrimentally impact population and economic health in low- and middle-income countries (LMICs).
^
5
^
^–^
^
7
^

EE probably represents a chronic adaptation of the proximal small intestine to marginal diets and exposure to environmental enteropathogens.
^
8
^ In LMICs, this adaptation develops in early life and is characterised by reduced absorptive surface area, goblet and Paneth cell depletion and intraepithelial lymphocyte infiltration.
^
9
^ Our work indicates that SAM is associated with a more severe enteropathy
^
10
^; a global disturbance of intestinal architecture and function, including maldigestion, malabsorption and impaired gut barrier function.
^
13
^ Impaired gut barrier function allows translocation of microbes and their products, which may explain systemic endotoxemia and, in some cases, sepsis and septic shock, which are major drivers of mortality.
^
11
^
^–^
^
13
^ Several non-invasive biomarkers of inflammation and microbial translocation have been proposed as biomarkers of severity of EE. Endotoxin core antibody (EndoCab), lipopolysaccharide (LPS) and myeloperoxidase (MPO) may be predictive of malnutrition status in children.
^
14
^ α-1-antitrypsin (AAT), MPO and neopterin, are elevated in malnourished children when compared to healthy children.
^
15
^ However, other studies do not report associations with malnutrition or lactulose-rhamnose tests.
^
16
^ These inconsistent associations hinder their broader application. Recent research in children with stunting has revealed significantly reduced HLA-DR expression on memory CD4+ and CD8+ T cells, along with a higher proportion of regulatory T cells and classical monocytes compared to non-stunted children.
^
17
^ Similarly, children with SAM exhibited lower HLA-DR upregulation on monocytes and neutrophils but demonstrated higher binding capacity for Escherichia coli than children without SAM.
^
18
^ These findings suggest an altered immune cell phenotype in children with SAM. Increased microbial metabolites, and acute phase proteins (CRP and calprotectin) and inflammatory markers were associated mortality in children with SAM.
^
19
^ These findings are further supported by another study which showed that markers associated with higher gut and systemic inflammation may be associated with higher mortality or hospital re-admission.
^
13
^ Additionally, biomarkers of environmental enteropathy (EE) may correlate with antigen-specific immune responses in SAM children at 18 months of age.
^
20
^ In the same study, maternal CRP and stool neopterin concentrations during pregnancy were associated with stronger heat-killed
*Salmonella typhimurium*-specific IL-8 responses in the children at 18 months. Furthermore, children who received water, sanitation, and hygiene (WASH) interventions demonstrated higher inducible LPS-specific myeloperoxidase (MPO) levels compared to those who did not receive such interventions. These findings underscore the complex interplay between the immune system, SAM, and EE. Further research is needed to better understand and differentiate the immune responses in SAM and EE, across both children and adults.

Both SAM and the antibiotic treatments recommended for children admitted to hospital with SAM also affect the gut microbiome, the composition of which is associated with lower bacterial diversity and maturity, which fail to persistently recover with standard nutritional therapies.
^
21
^ Characterization of the small intestinal microbiome in children is challenging due to the invasiveness of endoscopy procedures. Some studies showed through culture methods that small intestinal bacterial overgrowth (SIBO) is associated with stunting in children from Bangladesh,
^
22
^ Central African Republic and Madagascar. These studies also provided the first evidence, using 16s sequencing, of decompartmentalization of the microbiome along the GI tract in stunted growth and EE
^
23
^
^,^
^
24
^ and demonstrated a loss of carbohydrate-metabolising microbes in the small intestine.
^
25
^ These findings suggest that small intestinal microbes contribute to the pathophysiology of stunting however, these findings are relatively novel and need validation with different cohorts. There is a need to take a holistic approach to understanding the impact of undernutrition and EE on gut physiology across the whole gastrointestinal tract, which means developing tools for assessing multiple domains
^
26
^ of gut function (
Figure 1). This necessitates simultaneous assessment of the structure of the intestine (e.g. villus height, and therefore surface area), barrier function and microbial translocation, digestive and absorptive capacity (e.g., enzyme activity for protein, fat, and carbohydrate digestion, transporter expression for absorption), systemic, and intestinal immune responses to pathogens, expression of epithelial pattern recognition receptors (PRRs), pathogen-associated molecular patterns (PAMP; an indicator of microbial translocation), and the composition, function and metabolic activity of the gut microbiota. The latter will be reflected in the measured host metabolome. Such measurements will allow the selection of an optimised ‘toolkit’ for assessing gut functional capacity and ultimately enable the design of novel therapeutic feeds, which actively promote improved gut function, support sustained rehabilitation, reduce mortality, and feed the superorganism (i.e., the host and microbiome), and not just the host. Recent evidence has demonstrated that designing a diet to enhance normal maturation of the colonic microbiota results in improved growth
^
21
^
^,^
^
27
^
^,^
^
28
^ versus standard therapies in children recovering from acute malnutrition. Probiotic interventions have the potential to improve recovery and growth in various malnutrition disorders,
^
29
^ providing the proof-of-principle that rational design of feeds or biotherapeutics targeted to support gut function could be an achievable and effective therapeutic approach at scale.

**Figure 1. f1:**
[figure not shown]
Domains of intestinal dysfunction leading to cycle of inflammation and persistence. Illustration of prominent elements of inflammation cycle, that includes (i) changes to gut microbiota diversity and pathobiome colonisation leading to decompartmentalization, which promotes (ii) epithelial barrier failure leading to increased permeability and (iii) microbial translocation of cell wall antigens and bacteria, which stimulates (iv) mucosal inflammation leading to (v) systemic inflammation which leads to increased demands for essential nutrients (e.g. amino acids), whose bioavailability may be limited by (vi) maldigestion caused by alterations to brush border architecture and enzyme activity and (vii) malabsorption caused by changes to the expression of nutrient transport proteins in epithelial cells. At the present time, it is not possible to determine how this network of functions is interrelated, and which functions are critical to resolve without new tools to assess each of these domains.

The urgent problem which we aim to address in the GI Tools study is the dearth of measurement tools to assess the gut functional capacity of communities affected by EE. These tools will 1) be essential for evaluating gut functional capacity in adults (across many disease states) 2) have the potential to assess gut functional capacity in children because of their largely non-invasive nature, and 3) direct the development of new therapeutic interventions to support optimal gut function, for example, recovery of children hospitalised with SAM.

## Aims and objectives

The overarching objective of the GI Tools project is to develop a novel portfolio of tools for evaluating gut functional capacity in EE and malnutrition disorders. This protocol will allow for the determination of safety, acceptability, dosing, and timing for novel tools to evaluate gut functional capacity in adults with EE. This will be translated to work in malnourished children in further phases of this work.

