## Methods

### Study outcomes

The expected outcomes for each aim are shown in
Table 1.

**Table 1. T1:** Summary of outcomes with reference to study aims.

	Measured outcome	Detail
*Aim 1*	*Protein digestion and absorption using stable isotope tracers*	Assessment of ^13^C spirulina digestion (global index by breath ^13^CO _2_) and absorption using ^13^C Phe (from spirulina) and ^2^H labelled free Phe administered orally.
	*Bidirectional transmucosal amino acid flux (BTAAF)*	A novel tool involving dual infusion of differentially labelled amino acid tracers (Phe/Leu) orally and intravenously for the assessment of EE severity.
*Aim 2*	*Fluorescein*	A novel non-invasive measure of intestinal permeability using orally dosed fluorescein and a finger probe (transcutaneous fluorescence spectroscopy) for detection of systemically circulating fluorescein.
*Aim 3*	*Microbiome analysis*	I. Faecal species abundance and diversity indexes by 16s rRNA sequencing. II. In country deep metagenomic sequencing by long read (Nanopore) sequencing compared with other short-read platforms (Illumina). III. Evaluation of microbial communities in EE and their ability to uptake intestinal amino acids, including conversion of L-amino acids to D-forms.
	*Metabolic phenotyping*	I. Untargeted metabolomics ( ^1^H-NMR) of plasma, urine and faecal water. II. Targeted quantification (MS) of intestinal, plasma and urine amino acids (unlabelled + labelled) before and after administration of oral and intravenous stable isotopes.
	*Metaproteomic analysis*	1) Proteomic analysis of intestinal biopsies for expression of key mucosal proteins in biopsies (mucins and tight junction proteins including Zonulin, claudins and occludins). * 2) Dynamic proteomic analysis of key target proteins to assess mucosal and tight junction protein synthesis rates in biopsies by high-resolution MS and D2O labelling.
*Aim 4*	*Biomarker analysis*	Quantification of known markers of systemic inflammation, microbial translocation, and intestinal epithelial damage in plasma and stool.
	*Duodenal expression of PRR*	Profile the expression of bacterial, fungal, and viral PRR in the duodenal epithelium using immunohistochemistry.
	*Systemic immune cell analysis*	Characterisation of innate and adaptive systemic immune cell phenotypes using differential cell counting and flow cytometry.

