**Figure 2. f2:**
[figure not shown]
Study schema illustrating sample collection across the 4-day study period. Schema showing each sample collection time point throughout study, Day 1; No samples will be collected; Day 2; 9 mL heparinised blood; 2 mL EDTA blood; 5 mL citrated blood; 11 mL Urine at 00 and 180 mins; 4-8 g of stool; 0.5-2 mL of saliva at 00 and 180 mins; and breath samples every 20 mins. Day 3: 9 mL of heparinised blood; intermediate 2 mL heparinised blood samples every 20 mins for 1 h and every 30 mins for the last 2 h; breath samples every 20 mins; 0.5-2mL of saliva at 00, 60, 120 and 180 mins; 7 mL of urine at 00 and 180 mins; 4-8 g stool; 8 duodenal biopsies and 1 duodenal brushing; Day 4; 2-4 g of stool and 11 mL of urine.

### Day 1

This will include the final consent interview, administration of a questionnaire by the study nurse, clinical examination, and anthropometry (including weight, height, impedance, and deuterium approaches to body composition). Urine and stool collection devices will also be given.

### Day 2

Participants will bring urine and stool samples with them. Before administration of the solutions, a saliva sample, 9 mL of blood will be collected in lithium heparin, 2 mL in EDTA and 4.5 mL in citrated blood collection tubes, respectively, by venepuncture. A drink (prepared as shown in
Table 3) of
^2^H
_2_O (deuterated water, 1 g
^2^H
_2_O per kg body weight) containing
^13^C-spirulina protein (1.25 mg kg
^−1^) and (
^2^H
_8_)-Phe (0.035 mg kg
^−1^ in 200 mL clean water) will then be given at, or close to, 08:00 followed by breath sample collection using a straw and Exetainer tube (Labco, UK) every 20 mins for the first 1 h and every 30 mins for the remaining 3 h. A saliva sample will be collected at 180 mins, and a urine sample collection at 180 mins (3 h). A second drink of
^2^H
_2_O (1 g
^2^H
_2_O per kg body weight) will be given at 180 mins (3 h). During these procedures, a multi-pass 24-hour dietary recall will be administered by the study nurse. At the end of the procedures, the participant will be asked to fast after midnight and given stool and urine collection devices in readiness for day 3 procedures.

**Table 3. T3:** Composition of test solutions.

Solution	Composition	Administration
Solution A	• Deuterated water (D _2_O) (1 mL per kg body weight), • ^13^C-spirulina protein (1.25 mg kg ^−1^), and • ( ^2^H _8_)-Phe (200 mg) in 200 mL water	Oral, given at the beginning of day 2 procedures

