Solution B	• Deuterated water (D _2_O) (1 mL per kg body weight)	Oral, given at the end of day 2 procedures
Solution C	• ^2^H _5_-Phe (0.6 μmol kg ^−1^), • 5,5,5- ^2^H _3_-Leu (1.2 μmol kg ^−1^) made up to 10 mL with sterile filtered normal saline	Day 3, given intravenously as slow bolus at beginning of procedures
Solution D	• ^2^H _5_-Phe (0.15 μmol kg ^−1^) • 5,5,5- ^2^H _3_-leucine (0.3 μmol kg ^−1^) made up to 20 mL in sterile filtered normal saline	Day 3, given intravenously as continuous infusion over 3 hours
Solution E	• ^13^C _6_-Phe (0.6 μmol kg ^−1^), • ^13^C _6_-Leu (1.2 μmol kg ^−1^), • 5 g lactulose, • 1 g rhamnose, • 0.5 g D-xylose, • 0.2 g 3-O-methyl D-glucose, • 200 mg sodium fluorescein, • 1.667 mg L-arginine-(guanidineimino- ^15^N _2_) HCl, • 1.0 g glycyl sarcosine in 200 mL water	Day 3, given orally as bolus at beginning of procedures
Solution F	• ^13^C _6_-Phe (0.15 μmol kg ^−1^) • ^13^C _6_-Leu (0.3 μmol kg ^−1^) made up to 600 mL in clean water	Day 3, given orally as sips every 20 mins

### Day 3

Following an overnight fast, an intravenous cannula will be introduced into both arms and 5 mL of blood will be collected into a lithium heparin tube via cannula. The fingertip probe will be clamped gently onto a fingertip, and continuous fluorescence recordings will begin. An intravenous bolus of
^2^H
_5_-phenylalanine (0.6 mmol kg
^−1^) and 5,5,5-
^2^H
_3_-leucine (1.2 mmol kg
^−1^) in 10 mL normal saline filtered through a 0.2 mm syringe filter (solution C) will be given over 2 mins, and an oral bolus of
^13^C
_6_-leucine (1.2 mmol kg
^−1^),
^13^C
_6_-phenylalanine (0.6 mmol kg
^−1^), 5 g lactulose, 1 g rhamnose, 0.5 g D-xylose, 0.2 g 3-O methyl-D-glucose, 200 mg fluorescein, 1.667 mg L-arginine-(guanidineimino-
^15^N
_2_) HCl and 1.0 g glycyl sarcosine (solution E) given. A continuous intravenous infusion of
^2^H
_5_-phenylalanine (0.15 mmol kg
^−1^) and
^2^H
_3_-leucine (0.3 mmol kg
^−1^) (solution D) will be commenced, at 5 mL h
^−1^, and sips of
^13^C
_6_-phenylalanine (0.15 mmol kg
^−1^) and
^13^C
_6_-leucine (0.3 mmol kg
^−1^) (solution F) administered as sips every 20 mins (prepared as shown in

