Table 3). Breath samples will be collected every 20 mins for the first 1 h and every 30 mins for the remaining 3 h. Blood samples will be collected into lithium heparin collection tubes via the intravenous cannula: 2 mL every 20 mins for the first 1 h and every 30 mins for the remaining 3 h, and 5mL for the last sample. Urine will be collected up to 180 mins (3 h) while saliva collected every 60 mins for 3 h. After 240 mins (4 h) the participant will be transferred to the endoscopy room where upper gastrointestinal endoscopy will be performed using doses of sedation with midazolam and pethidine selected by the endoscopist. Oximetry will be used throughout the procedure. During endoscopy, up to 10 mL of duodenal aspirate will be collected with clean tubing. Using the same tubing, 20 mL 0.9% of sterile saline will be used to collect duodenal lavage. A brushing will be collected using an endoscopic cytology brush, and then the brush will be cut off into 1000 μL PBS. For histology, 3 biopsies will be collected into normal saline using 2.8 mm biopsy forceps, orientated on cellulose acetate paper (Sartorius, Gottingen, Germany) in the endoscopy room and placed in formalin thereafter. An additional 5 biopsies will be collected into 3 cryovials (2+2+1). All samples collected during endoscopy, except for the 3 histology biopsies, will be snap-frozen in liquid nitrogen immediately after collection. At the end of day 3, the participant will be given urine and stool collection devices for the next day.

### Day 4

Only stool and urine samples will be collected.

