## Colonoscopy: Zimbabwe

An intravenous injection of a single dose of 600 mg benzylpenicillin will be given in patients presenting for colonoscopy, 10 – 15 minutes before the procedure. Luminal fluid from the right side of the colon will be aspirated between 20 and 40 mins after benzylpenicillin administration. This fluid will be centrifuged, stored, and shipped to Imperial College where the assays for the presence of benzylpenicillin, which will indicate reverse permeation, will be performed. This sub-study is directed at understanding whether the degree of barrier loss in environmental enteropathy is sufficient to permit leakage of antibiotics into the right colon. Penicillin was selected as it is a narrow-spectrum antibiotic which would not be expected to cause significant microbiome disruption in these healthy volunteers, which might be an ethical concern. A recent study
^
37
^ showed that antibiotic secretion into bile can modulate the microbiota during cardiac surgery, but this is a situation where gut hypoperfusion is well known to drive barrier failure. Such effects have not, to our knowledge, been shown in EE.

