## Sample handling

Samples for safety analysis (differential blood count using the Sysmex XP300™ automated haematology analyser (Sysmex UK Ltd., Milton Keynes, UK) and prothrombin time using the HumaClot Junior (HUMAN Diagnostics Worldwide, Wiesbaden, Germany)) will be processed immediately; excess samples will be retained as backup, but destroyed once the study is complete. Samples for research assays (
Table 4) will be analysed immediately or stored at appropriate temperatures (usually -80°C). Blood samples from Day 2 (9 mL) will be centrifuged (2,300
*g* for 5 minutes at 4°C) to separate plasma from buffy coat cells (enriched for immune cells) and red blood cells; plasma will be aliquoted and stored at -80°C and buffy coat cells will be treated to lyse red blood cells, fixed, washed, re-suspended in cell preservation media, and cryopreserved gradually to -80°C using cell freezing containers to maintain cell integrity. On day 3, blood collected at different time intervals in lithium heparin (
Table 4) will be centrifuged under the same conditions to separate plasma which will be aliquoted and stored at -80°C. Stool samples collected on days 2, 3 and 4 will be aliquoted and stored at -80°C. All saliva samples collected on days 2 and 3, all urine and stool samples collected on days 2, 3, and 4 will also be aliquoted and stored at -80°C. All breath samples that will be collected on days 2 and 3 will be stored at room temperature until analysis. All cryo-stored samples will be retained until batch analyses at either TROPGAN or may be shipped to the relevant external laboratories for analyses (shown in
Table 4). For sample types being shipped for analyses at external laboratories, an aliquot of each will be retained at TROPGAN wherever possible; these aliquots will act as a backup in case of analytical failures, or storage failures during transport to another laboratory.

**Table 4. T4:** Summary of laboratory analytical methods.

Sample Type	Assays	Methods	Study participants	Time-points
Stool	Microbiome sequencing	Illumina HiSeq, MinION	All	Baseline
	Barrier integrity and function	Epithelial cell co-cultures		Baseline or Day 2
	Biomarkers	ELISA		Baseline
	Immune signalling assays	Reporter cell line co-culture		Baseline or Day 2
	Dynamic proteomics	LC-MS/MS		Day 3, Day 4
	Metabolic phenotyping	NMR spectroscopy		Day 2, Day 3
Urine	Metabolic phenotyping	NMR spectroscopy	All	Baseline
	Targeted isotope analysis	LC-MS/MS		Day 1, Day 2

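### The protocol says it will determine dosing, but each administered agent is planned at one level only, and neither the aims nor Table 1 names a safety or acceptability outcome

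*Protocol article*

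**What the plan says.** The objective, under Aims and objectives, reads: "This protocol will allow for the determination of safety, acceptability, dosing, and timing for novel tools". It refers to adults with EE, and the next sentence says the work will be carried forward to malnourished children in further phases.

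Outcomes are listed in Table 1, titled "Summary of outcomes with reference to study aims". Its entries are tracer, permeability, microbiome, metabolic, proteomic, immune and antibiotic measurements, plus their comparison with histology, sugar permeability testing and EE biomarkers. The list under Study aims has the same scope.

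Table 3 gives the composition of solutions A to F. Each ingredient has one amount, either flat or per kg body weight, for everyone. Solution E, for example, contains "200 mg sodium fluorescein" among nine agents and is "Day 3, given orally as bolus at beginning of procedures".

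The article does mention safety specimens under Sample handling: "Samples for safety analysis (differential blood count using the Sysmex XP300" and so on, together with prothrombin time.

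**The concern.** The objective names four things the study will establish about the tools. A reader planning the next phase would take each as a result to build on. If the design yields only one of them, and the outcome list is silent on two others, the final report may claim more than its data can support.

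Dosing is the clearest case. To determine a dose, a study needs at least two levels to compare, or a rule that moves from one level to another. For safety and acceptability, a named and scheduled measure is needed. Without one there is a denominator but no defined numerator, and an absence of reported problems cannot be told apart from an absence of questions.

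**Working it through.** No stated figure has to be reproduced, because neither sample-size calculation (breath test and circulating LPS) concerns safety, acceptability or dosing. The check sets the four parts of the objective against the procedures.

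**Timing: supported.** On Day 3 fluorescence is recorded continuously. Blood is taken every 20 min for 1 h and every 30 min for 3 h, which is 3 + 6 = 9 samples after baseline over 4 h. Breath is sampled on the same pattern on Days 2 and 3.

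**Dosing: not supported.**
- Levels per agent in Table 3: 1. Between-dose contrasts: 1 − 1 = 0.
- Per-kg amounts remove even incidental variation in relative dose. Flat amounts (fluorescein, the sugars, the dipeptide) do vary per kg between participants, but that variation is body weight itself. It is not assigned, and it cannot separate dose from body size.
- No earlier dose-ranging stage or escalation rule is described.

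Some of the single levels are also stated in conflicting ways. These are contradictions, not planned dose arms:
- Labelled phenylalanine on Day 2: Table 3 has "Phe (200 mg) in 200 mL water", while the Day 2 text has 0.035 mg per kg. The two agree only at a body weight of 200 / 0.035 ≈ 5,714 kg, so rounding does not explain the gap.
- Amino acid tracers on Day 3: μmol per kg in Table 3, mmol per kg in the Day 3 text, a factor of 1,000. This may be a typesetting artefact and should be checked on the published page.
- Deuterated water: 1 mL per kg in Table 3, 1 g per kg in the Day 2 text.

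**Safety: no named outcome.** Table 1 has none. The safety specimens are a blood count and a clotting test. The tubes that fit these tests (EDTA and citrate) are drawn on Day 2 before the first drink. Day 3 blood is described as lithium heparin only. Table 4 dates haematology as baseline or Day 3. A Day 3 sample would follow the Day 2 solutions, but no suitable tube is described for it. As written, these look like checks before endoscopy rather than evidence on the tools.

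**Acceptability: no named outcome.** Withdrawal is permitted without replacement but is not designated as an acceptability measure.

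**What the sample could show if events were recorded.** The exact one-sided 95% upper limit for 0 events in n is 1 − 0.05^(1/n):
- n = 80 (adults with EE): 1 − 0.05^(1/80) = 0.0368, or 3.7%.
- n = 30 (the number the sample-size section gives for its definitive studies): 1 − 0.05^(1/30) = 0.095, or 9.5%.

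With n = 80, the chance of seeing at least one event is 1 − (1 − p)^80: 55% if the true rate p is 1%, 80% at 2% and 98% at 5%. Descriptive safety is therefore within reach.

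**Separating sources of symptoms.** Solution E mixes nine agents and is given alongside intravenous tracers. Sedation and eight biopsies (3 + 5) follow the same day, but only after 240 min. That interval allows tracer symptoms to be recorded before endoscopy. It does not allow one ingredient of the mixture to be separated from another.

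**The case against.** The strongest reply is that this is a journal article. Adverse-event forms and acceptability questions commonly sit in the full protocol, and their absence here does not show that they will not be used. That stands, and it limits the safety and acceptability part to a mismatch between the stated objective and the stated outcomes. It does not rescue dosing, because the solutions and daily procedures are given in detail and show one level each.

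A second reply is that Table 1 follows the numbered aims, which make no safety or dosing claim, so the conflict is confined to one framing sentence. That is fair, but the sentence is the overarching statement of what the protocol delivers.

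A third is that dosing may mean only that the chosen amount gives a measurable signal. The study can show that, and the wording should then say so.

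Three stronger readings are tempting and are not supported:
- **That Day 4 rules out safety follow-up.** The Day 4 entry reads "Only stool and urine samples will be collected". It is a list of specimens. The Figure 2 legend likewise says that no samples are taken on Day 1, yet Day 1 has a questionnaire, a clinical examination and anthropometry.
- **That the Harare sub-study shares the fault.** There, "An intravenous injection of a single dose of 600 mg benzylpenicillin will be given in patients presenting for colonoscopy". This too is one level, but the objective concerns adults with EE, whereas the Harare participants are patients of higher socioeconomic status already booked for colonoscopy. Any gap in contact after the procedure would be inferred from silence.
- **That the whole objective cannot be met.** Timing can be, and safety and acceptability may be covered elsewhere.

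**Conclusion.** The point holds in limited form. Dosing is a property the design does not have: with one level per agent there is no contrast, and the result is feasibility and signal detectability at that level. Safety and acceptability are claimed in the objective but unsupported by the aims and outcome list as written. The specimens labelled for safety do not fill the gap, on the assumption that they are the EDTA and citrate tubes drawn before dosing on Day 2.

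The sample is large enough for a useful descriptive statement. Zero events among 80 adults with EE would exclude rates above 3.7% (one-sided 95%), provided all 80 receive the tool and are asked. If a tool is given to only 30, the limit is 9.5%.

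The practical weight is moderate. Work in children is deferred to later phases, so the article does not present this study alone as sufficient, but those phases are meant to build on it.

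**What to change.** 1. In Aims and objectives, replace the dosing claim with feasibility and signal detectability at the single planned level. Reconcile the passages that state those levels differently (labelled phenylalanine, the Day 3 amino acid tracers, deuterated water). This review takes no position on which figure is right.
2. For safety and acceptability, do one of the following:
   - Add solicited symptoms and a short acceptability score to Table 1, recorded at attendances that already exist: the end of Day 2, and Day 3 after the last tracer sample and before sedation. Report proportions with exact confidence limits, and attribute events after solution E to the mixture rather than to single ingredients.
   - If the full protocol already has such measures, name them in Table 1.
   - Otherwise narrow the objective so that it does not claim to determine safety and acceptability.
3. State when the blood count and prothrombin time are drawn relative to the test solutions and what they are for.

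The cost is a few minutes per attendance, a narrower stated claim, and a protocol amendment submitted to the approving bodies if new outcomes are added. No extra visit or procedure is needed.
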